#### Per-protocol analysis

If the per-protocol sample set differs from the ITT sample set, the primary analysis on the first-time infection and the secondary analysis on the overall infections will also performed in the per-protocol sample set.

### Methods in analysis to handle protocol non-adherence and any statistical methods to handle missing data {20c}

Standard Operating Procedures have been developed for all study activities, to include reporting Protocol Deviations and Protocol Violations. A Clinical Monitoring Plan has been established among the Sponsor, trial implementing partner, and the project clinical research organization—fhiClinical. fhiClinical will be responsible for managing oversight on protocol adherence through interim monitoring visits during the study phase. Departures from the protocol that are not participant-specific will be documented on a Protocol Deviation log developed by KEMRI and reported as required, and the site re-educated as necessary. Any participant-specific non-compliances and other protocol deviations will be captured in the protocol deviation Case Report Form developed by KEMRI and filed as hard copies. Major protocol deviations are to be submitted via email to applicable IRBs and the Sponsor within 24 h of the Site PI becoming aware of them, and followed by a detailed report, within 7 working days.

Significant effort will be made to avoid having missing values on outcome (malaria infection status and visit dates, and entomological endpoints). When missing values occur for an outcome for reasons not related to the outcome, reasons for missingness and the missing fraction by treatment arm and cluster will be reported. Per protocol, the subjects are screened actively on their malaria status (the outcome) every 4 weeks.

If a subject misses one or more scheduled visits due to reasons not related to the SR product or the outcome, the subject will have missing values on the outcome that can be regarded as ignorable missingness (missing at random or missing completely at random). If a subject drops out of the study due to reasons unrelated to the SR product and/or malaria infection, then the missing observations from the subject can be regarded as ignorable missingness. In both cases, all available data from the subject will be included in the primary and secondary analysis, without employing any specific technique to deal with the data, due to the ignorability of the missing mechanism.

Missing baseline covariates (individual level, household level, and cluster level) that are a part of the regression models for the outcome of interest will be imputed using simple hot-deck imputation methods if the missing fraction for the covariate is < 5%. If the missing fraction for a covariable are ≥5%, appropriate multiple imputation approaches will be applied. If a non-ignorable portion of the subjects have missing values on a covariate (due to missing at random or missing completely at random), that covariate may be excluded in the model.

### Plans to give access to the full protocol, participant-level data, and statistical code {31c}

The statistical analysis plan and analytic code will be made open access. The data and supporting information will be made available 12 months following completion of data analysis and will remain open access in the public domain.

## Oversight and monitoring

### Composition of the coordinating center and trial steering committee {5d}

UND serves are the lead organization and assumes the overall responsibility for management, oversight, and administration for the program. The coordinating personnel at UND include the Lead PI, Scientific Director, Program Manager, Program Coordinator, and Finance Manager. UND communicates on a day-to-day basis with KEMRI and CDC. KEMRI is responsible for running the cRCT on a day-to-day basis which includes but is not limited to conducting a baseline survey, deploying SRs, entomological monitoring, and subject follow-up. CDC provides technical support for the entomological and epidemiological aspects of the study. Representatives from KEMRI, CDC, and UND serve on the data management team overseeing the development and implementation of data collection, recording, and cleaning. UND will rely on fhiClinical to provide clinical oversight and monitoring of study processes, which includes but is not limited to checking enrolment, training of staff on GCP, ensuring subjects are properly consented, data are appropriately gathered, data quality, safety events are documented and reported as required, investigational product is stored, distributed and managed per specifications, and study close-out activities occur on a timely basis.

### Composition of the data monitoring committee, its role, and reporting structure {21a}

The DSMB reviews data about the safety of the Kenya cRCT and the test articles and makes recommendations about stopping the study for safety reasons. Additionally, the DSMB provides additional credibility about study quality, by reviewing regular (summary) reports from PIs during baseline and intervention phases and making recommendations as needed about study adjustment for study quality reasons. The DSMB consists of a Chair, Medical Monitor, DSMB biostatistician, and independent statistician. Members generally have no ongoing financial relationship with a trial’s commercial sponsor and will not be involved in the conduct of the trial in any role other than that of a DSMB member. Prospective members will be asked to disclose their financial relationships with any of the sponsors and/or their competitors. The DSMB reports to the Sponsor, UND. The DSMB charter can be made available upon request to UND.

### Adverse event reporting and harms {22}

The SR product contains transfluthrin, a chemical used in currently available HH mosquito control products such as mosquito coils. Exposure to the product may cause mild eye and skin irritation. These effects are usually transient and disappear after time. The product may be harmful if chewed on or swallowed, so HH owners will be advised to keep it away from children. The SR product will be fixed at a position that is out of the reach of children and it will be monitored at replacement to ensure it has not been moved. If a product is found to have been removed from its position in the HH, study staff will discuss with the HH owner to determine why it was removed and if there was any problem that led to its removal. Study staff will also reiterate safety precautions that should be taken in regard to the SR product.

AEs and SAEs of interest will be collected through passive surveillance by CHVs on children enrolled in the cohort and on other HH members who receive the study product. Additionally, AE and SAEs of interest will be solicited from study participants during follow-up visits (every 2 weeks) either in the house or clinic. We will also rely on passive surveillance of the outpatient registers at the local health facilities for reports of AE/SAE. Additionally, we may also collect unsolicited reports during compound visits and/or product replacement. Anyone experiencing the SAEs or AEs of interest will be encouraged to seek care for at the study clinic where our clinical staff will attend to them at no cost.

Unexpected SAEs affecting the cohort participants determined to be at least “possibly related” will be reported to the KEMRI SERU, study sponsor at UND, and Independent DSMB within 24 h of the PI becoming aware of the SAE. The initial report will be a short description by email, which will be followed within 7 days by a more detailed description of the SAE. AEs of interest considered at least “possibly related” will be reported to the same groups on at least an annual basis.

An AE or suspected AE is considered “serious” if it meets the following conditions:
Results in deathIs immediately life-threateningRequires in-patient hospitalization or prolongation of existing hospitalizationResults in persistent or significant disability or incapacityResults in a congenital abnormality or birth defectIs an important medical event that may jeopardize the patient or may require medical or surgical intervention to prevent one of the outcomes listed above

All SAEs starting from enrolment until the last contact with the participant, whether or not they are related to the study product, will be reported.

AEs and SAEs during the trial will be reported in future publications. Harms will be coded in accordance with MedDRA at time of safety outcome reporting. Summary of symptom-based AE, SAE, and death reports observed during the studies will be reviewed by the trial DSMB at predetermined checks (quarterly). The AE/SAE will be labelled “Probable,” “Possible,” “Plausible,” or “Unlikely” due to SR. Summary statistics of AEs/SAEs, including mean, minimum, and maximum frequencies and percentages across clusters among enrolled subjects, will be provided by treatment arm. Statistical comparisons of the AE/SAE rates between the two arms will be conducted upon the completion of the study. Two sets of statistical analysis will be run. One set will compare the proportion of having at least one occurrence in each symptom-based AE/SAE during the whole study between the two arms, and the other will compare the total number of occurrences for each AE/SAE between the two study arms. If the data collected permits meaningful statistical hypothesis testing, *p*-values from the treatment comparisons will be reported, with multiplicity correction via the FDR approach [44].

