For product application, all HHs within the selected clusters will be eligible to receive intervention. Informed consent from heads of HH, or spouse, will be sought for application of product in the home. Heads of HH will also be consented for mosquito light trap and HLC collections inside and/or outdoors of their homes. HH with child subjects enrolled for malaria incidence follow-up will be excluded from HLC collections. Adult males residing in consenting homes will be recruited to serve as mosquito collectors. The collectors will be asked to stay up throughout the night collecting mosquitoes that land on their exposed legs. An ICF will be obtained from the collectors.

All ICFs will include informing participants to report to a study clinic if experiencing an adverse event (AE) to be assessed and receive essential, point of care treatment free of charge whether or not the event is subsequently determined to be study related. They will only receive enough treatment to ensure they are not disadvantaged, clinically or financially, by going first to the study clinician instead of regular Ministry of Health (MOH) staff. They will not, however, receive free, comprehensive treatment for any illness found to be unrelated to study procedures (product, medicines). The ICF will also inform participants if anyone in their house becomes severely ill, they should go immediately to the nearest health facility.

Copies of informed consent documents will be made available upon request to the AEGIS Program Manager ([contact]).

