At each visit, the parent/guardian will be asked about recent use of ITNs and other vector control interventions as well as recent history of child’s illness and recent use of anti-malarial drugs. At every clinic visit (on a monthly basis), a blood smear will be taken for malaria diagnosis. An RDT will be taken if the participant has a recent history of fever. At the intervening home visits, a blood sample will only be taken if the child has a recent history of fever or other symptoms attributable to malaria infection. Total blood volume for samples at each visit will not exceed 500 μL.

Cohort children who test positive for malaria by RDT will be treated with AL free of charge. Blood slides of children who test negative by RDT will be prioritized for examination, and treatment will be provided based on a single positive reading. However, the endpoint measurement for formal analysis will be based on examination of all blood slides by at least two expert microscopists with any discordant results resolved by a third. Cohort children will be provided a transport reimbursement for monthly scheduled clinic visits to offset the cost of coming to the clinic. Transport to hospital, if needed, will be facilitated through transport reimbursement. If there is illness or injury due to study products or procedures, fees will be paid for care at the government clinic or county or referral hospital. Referrals will be done using the general referral form. If the level of care necessary of the illness/injury is not available at the government hospital, the study will pay for care at a private health facility.

Cohorts will also be enrolled to estimate the diversionary effect of the SR intervention. Children in this cohort will be recruited from buffer zones surrounding each cluster. HHs in this area will not receive the SR or the placebo but recruitment, enrolment, screening, and follow-up procedures will be the same as described.

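### The two main SAE collection channels are worded for SAEs 'of interest', which is narrower than the protocol's own commitment to report all SAEs

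*Protocol article*

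**What the plan says.** Under *Adverse event reporting and harms {22}*, the protocol article describes two main ways of collecting safety events, both with the same qualifier:

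- Community health volunteers: "AEs and SAEs of interest will be collected through passive surveillance by CHVs on children enrolled in the cohort". The sentence goes on to include other members of households that receive product.
- Scheduled visits: "AE and SAEs of interest will be solicited from study participants during follow-up visits (every 2 weeks) either in the house or clinic".

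The same paragraph adds two sources without the qualifier: "We will also rely on passive surveillance of the outpatient registers at the local health facilities for reports of AE/SAE", and "we may also collect unsolicited reports during compound visits and/or product replacement".

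After listing general seriousness criteria, the section sets the reporting rule: "All SAEs starting from enrolment until the last contact with the participant, whether or not they are related to the study product, will be reported".

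*Outcomes {12}* names AEs and SAEs as a secondary outcome, measured by both solicited and unsolicited reports, with no restriction to a list.

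**The concern.** Whatever the list contains, 'SAEs of interest' and 'all SAEs' are different sets. The first governs what volunteers and visit staff are told to look for. The second governs what must be reported. A reporting rule does not by itself find events. If the scheduled questioning covers only part of the set, the rest depends on routes that are less regular.

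This bears on the by-arm SAE summaries, the planned between-arm comparison of AE and SAE rates, and the quarterly DSMB review. An unexpected serious event is also the kind that a list drawn up in advance is least likely to name. The expedited 24-hour report for unexpected, possibly related SAEs starts only once the investigator knows of the event.

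**Working it through.** No arithmetic applies: the article states no SAE rate and no expected count, so there is no figure to reproduce. The check is a comparison of every route by which an SAE in an enrolled child could come to notice.

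| Route | Section | Limited to 'of interest'? | Remark |
|---|---|---|---|
| Volunteer surveillance | Harms {22} | Yes | Passive |
| Solicitation at visits every 2 weeks | Harms {22} | Yes | The only safety channel described as asking every enrolled child on a fixed schedule |
| Outpatient registers | Harms {22} | No | May not show deaths or in-patient admissions |
| Unsolicited reports | Harms {22} | No | Optional: worded with 'may' |
| Self-report to the study clinic | Informed consent {26a} | No | "All ICFs will include informing participants to report to a study clinic if experiencing an adverse event (AE) to be assessed" |
| Unscheduled sick visits | Cohort follow-up | No | At a study facility, or at home if the child cannot reach it |
| Illness history at each visit | Cohort follow-up | No | Parent or guardian asked about ITN and vector control use "as well as recent history of child’s illness and recent use of anti-malarial drugs"; not tied to AE/SAE recording |

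1. Of the seven routes, two carry the limit and five do not.
2. The two that carry it include the one scheduled safety enquiry. That is where the mismatch with the all-SAE rule matters most.
3. The five unrestricted routes are real but uneven. One is optional and one is confined to outpatient records. Self-report points families to the study clinic, yet the same consent section directs anyone severely ill to the nearest health facility, so the gravest cases may be seen elsewhere first. Illness history would probably reveal some SAEs, but the article does not say that an answer there opens an SAE record.
4. The qualifier is probably not a single slip. It appears in both collection sentences and again in the sentence that encourages affected people to seek care at the study clinic.
5. The all-SAE sentence and the Outcomes text agree with each other. The two collection sentences are the ones out of line.

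**The case against.** The strongest reply is that the text describes a prompted list together with an unprompted net. That is how Outcomes {12} defines the measurement, and it is a common arrangement. On this reading, 'of interest' only shapes the prompts. The all-SAE rule, with seriousness defined by general criteria and not by a list, still obliges staff to report anything serious they learn of. Unexpected SAEs are expressly provided for, both in the 24-hour reporting rule and in the emergency unblinding procedure. Children are seen or contacted every two weeks, those who miss appointments are traced, and hospital transport and referral pass through the study, so staff would hear of many admissions.

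Much of this stands. A reader might infer that the trial collects only listed events, that SAEs off the list would go uncaptured, or that the SAE outcome will be incomplete. The documents do not support any of these, because five routes are unrestricted and the duty to report all SAEs is explicit. The lack of a definition of 'of interest' is no fault either, since a journal article may leave it to the full protocol.

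What the reply does not remove is the mismatch. The collection sentences apply the qualifier to SAEs as well as AEs, and none of the unrestricted routes is stated to secure all SAEs.

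**Conclusion.** There is an inconsistency in SAE scope within the harms section, and between its collection sentences and Outcomes {12}. Its consequence is a possible risk of less systematic capture of SAEs outside the list.

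The size cannot be estimated. A reader might be tempted to put a count on missed events by multiplying child-years by an SAE rate and by the share not on the list. The article gives neither the rate nor the share, and such a product would also assume that every unrestricted route fails. Nor would all children in it bear on product safety. Table 1 has 2 × 2040 = 4080 children in the two intervention cohorts, of whom 2 × 1200 = 2400 live in buffer zones where households receive neither product. Only 2 × 840 = 1680 live in treated core areas.

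Nothing suggests that under-capture would differ by arm: participants, investigators and staff are blinded, and the procedures are common to both arms. Equal under-capture would still lower the observed rates in both arms and weaken the safety comparison. The conclusion assumes that the qualifier means what it says in the two sentences. If it is loose wording, the correction costs nothing.

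**What to change.** Reconcile the two collection sentences in Adverse event reporting and harms {22} with the all-SAE sentence in the same section. Delete 'of interest' as it applies to SAEs in the volunteer-surveillance sentence and in the scheduled-visit sentence, so that any SAE is asked about and recorded at each scheduled visit from enrolment to last contact. Leave Outcomes {12} and the scope for non-serious AEs unchanged; narrowing the Outcomes text to match would create a new problem.

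One detail to settle while editing: the volunteer sentence also covers other members of treated households, whereas the all-SAE sentence speaks of the participant. The sponsor should state whether the wider SAE scope extends to those household members.

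The cost is wording in the protocol, carried into the visit form and the volunteers' instructions where needed. The extra recording is small, and for enrolled children it adds no commitment beyond the one already made to report all SAEs.

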### Trial design {8}

An outline of the trial design and sample size is summarized in Table 1. This study is a cluster-randomized controlled trial (cRCT) with 30 clusters per treatment arm (SR and placebo), consisting of 4 months of baseline data collection and after baseline, two independent cohorts enrolled (cohort 1 and cohort 2) and each followed for 12 months for a total of a 24-month follow-up with intervention.

**Table 1 Tab1:** Outline of the cluster design and sample size for the SR cRCT in Busia County, Kenya

Cluster design	Baseline cohort	Intervention cohorts		
	4-month follow-up (*n* = 2040)	Time of intervention deployment	12-month follow-up (cohort 1) (*n* = 2040)	12-month follow-up (cohort 2) (*n* = 2040)
**Core area** 60 clusters total	20 subjects per cluster 1200 subjects total	Year 1	SR (30 clusters), Placebo (30 clusters) 14 subjects per cluster 840 subjects total	n/a
		Year 2	n/a	SR (30 clusters), Placebo (30 clusters) 14 subjects per cluster 840 subjects total
**Buffer zone** 60 clusters total	14 subjects per cluster 840 subjects total	Year 1	SR (30 clusters), Placebo (30 clusters) 20 subjects per cluster 1200 subjects total	n/a
		Year 2	n/a	SR (30 clusters), Placebo (30 clusters) 20 subjects per cluster 1200 subjects total

For the evaluation of the primary epidemiological objective (PE), a total of 28 subjects (HHs) will be recruited from each core area of a cluster or equivalently 14 subjects (HHs) per cohort per cluster (factoring in a 35% loss-to-follow-up (LTFU) rate). For the evaluation of the secondary epidemiological objective on SR diversionary effect, a total of 40 subjects (HHs) or equivalently 20 subjects (HHs) per cohort per cluster will be recruited from each buffer zone (factoring in a 35% LTFU rate). At least one child aged ≥ 6 months old to 9 years and 11 months old from each HH will be recruited for biweekly (every 2 weeks) malaria check-ups during the follow-up period with intervention.

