### Criteria for discontinuing or modifying allocated interventions {11b}

If a participant chooses to discontinue participation in the study, study staff will respect the decision without penalty. Study staff may terminate subject participation at any time during the trial, as needed, if a subject no longer meets the inclusion criteria and/or based on AE and/or SAE clinical assessment.

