#### Primary hypothesis on first-time malaria infection

The sample size determination on the required number of subjects (HHs) per cluster for testing the primary hypothesis is based on the hazard rate comparison in the proportional hazards regression model [36, 37]. With the following specifications: 1-sided type I error rate = 5%, true PE = 30%, a between-cluster CV of hazard rate = 44% (based on historical data collected from Kenya), one interim analysis for efficacy and non-binding futility with the O’Brien-Fleming error spending function when 50% of events have been collected then 1055 first-time malaria events will need to be observed to reach 85% power in testing the primary hypothesis on PE.

With a baseline first-time malaria infection hazard rate of 3.0 per person-year, 30 clusters per treatment arm, with 20 subjects (HHs) per cluster are expected to yield 1055 independent first-time malaria events within a 12-month follow-up period per cohort post randomization to yield 85% power. If, by the end of the 2-year study, 1055 independent malaria events are not reached, the study may extend until 1055 events are collected without inflating the type I error rate in the testing of the primary hypothesis. Factoring in a LTFU rate at 35%, the required sample size is 28 subjects (HHs) per cluster, which will be split in half between the two sequential cohorts with 14 subjects (HHs) per cohort per cluster.

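### The harms comparison is introduced as one of rates but is fixed as a crude proportion and a crude total, neither using time under observation

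*Protocol article*

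**What the plan says.** In the protocol article, Adverse event reporting and harms {22} opens the analysis with "Statistical comparisons of the AE/SAE rates between the two arms will be conducted upon the completion of the study". It then names two analyses. For the first, "One set will compare the proportion of having at least one occurrence in each symptom-based AE/SAE during the whole study between the two arms"; for the second, "the other will compare the total number of occurrences for each AE/SAE between the two study arms". P-values, with a false-discovery-rate correction, follow if the data allow testing.

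Other sections show that children will be observed for different lengths of time:

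- Trial design {8} sets recruitment "factoring in a 35% loss-to-follow-up (LTFU) rate". The sample-size section on the primary hypothesis repeats it: "Factoring in a LTFU rate at 35%, the required sample size is 28 subjects (HHs) per cluster".
- Criteria for discontinuing or modifying allocated interventions {11b} lets staff end a child's participation "if a subject no longer meets the inclusion criteria and/or based on AE and/or SAE clinical assessment".
- The harms section sets the SAE reporting window as "All SAEs starting from enrolment until the last contact with the participant", so it closes when the child leaves.
- The missing-data text in {20c} lists malaria status, visit dates and entomological endpoints as the outcomes it covers. It does not name adverse events. It treats as ignorable only dropout unrelated to the product or to malaria.

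**The concern.** A proportion over the whole study and a total count both depend on how long each child was watched. A child who leaves event-free early is scored like a child observed event-free for 12 months. A child withdrawn "based on AE and/or SAE clinical assessment" adds no further occurrences. Neither measure is a rate in the sense that the lead-in suggests, and the section does not say how partial follow-up is handled.

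The efficacy analysis of the same children uses time-to-event models with a cluster random effect, so the harms comparison is the less careful of the two. At stake is the safety conclusion that accompanies the efficacy result to the WHO advisory group. If time observed differed between arms, the planned comparisons would mix that difference with any difference in AE risk.

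**Working it through.** The document gives no numerical figure for the harms comparison, so there is none to reproduce.

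**Inputs from the document:** 12 months of follow-up per child; 35% loss, given as one overall allowance and not by arm; AE-based withdrawal permitted in both arms.

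**Assumed inputs (none are in the document):** constant AE rate r per child-year; exponential dropout; probability q that an AE ends participation; any split of loss by arm.

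**Formulas** (one year, loss L):
- Dropout hazard d = −ln(1 − L). At L = 0.35, d = 0.431.
- Mean time observed T = (1 − exp(−(d + rq))) / (d + rq). With q = 0 this is L / (−ln(1 − L)).
- Expected occurrences per child = r × T, so count ratio = true rate ratio × (T on repellent / T on placebo).
- Proportion with at least one AE = r/(r + d) × (1 − exp(−(r + d))).

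**1. Equal loss of 35%.** T = 0.35/0.431 = 0.81 year in both arms, so the T ratio is 1 and the count ratio equals the true ratio (1.25 reads as 1.25). Proportions at r = 1.0 and 1.25:
- No loss: 0.713/0.632 = 1.13.
- 35% loss in both arms: 0.605/0.532 = 1.14.

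At a placebo rate of 0.05 per year the proportion ratio is 1.24 with or without the loss.

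**2. AE-triggered withdrawal, same q in both arms.** True rates 1.0 and 1.5, d = 0.431:

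| q | Occurrences per child, placebo | Occurrences per child, repellent | Count ratio |
|---|---|---|---|
| 0.2 | 0.742 | 1.064 | 1.43 |
| 0.5 | 0.651 | 0.880 | 1.35 |

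The ratio shrinks toward 1 and does not cross it. The proportion for the AE that caused the withdrawal is unaffected, because the child has already had that AE.

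**3. Loss that differs by arm, q = 0, equal AE rates.**

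| Loss, repellent / placebo | T, repellent / placebo | Count ratio |
|---|---|---|
| 40% / 30% | 0.783 / 0.841 | 0.93 |
| 45% / 25% | 0.753 / 0.869 | 0.87 |

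At 45%/25% and r = 1.0, the proportion ratio is 0.499/0.562 = 0.89. A true 10% excess on repellent then reads as 1.10 × 0.866 = 0.95 on counts, and as 0.94 to 0.95 on proportions. The count ratio is below 1 for any true ratio under 1/0.866 = 1.15 (1.13 if losses are uniform in time). For 40%/30% that limit is 1.07 (1.06 if uniform).

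**4. Rate per time observed.** Since occurrences = r × T, dividing by T returns r in each scenario above. This holds if dropout is unrelated to unobserved AE risk.

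**The case against.** A reader might infer that the 35% loss, or the AE-withdrawal rule, is enough to make a harmful product look safer. The documents do not support that. Step 1 shows that equal loss does no such thing. Step 2 shows that one withdrawal rule applied alike in both arms only dilutes the count ratio, so a product that causes more AEs still shows more.

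Reversal needs loss, or a withdrawal probability, that differs by arm. If AEs ended participation only on repellent (q = 0.5, placebo rate 1.0), a true ratio of 1.25 would read as 0.95. The withdrawal rule is the same in both arms, the trial is blinded with matched products and one visit schedule, and the expected effects are described as mild and usually transient. Nothing in the document predicts such a difference.

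Two further points carry weight. Adverse events are also sought through community health volunteers and outpatient registers, so some events after cohort visits stop may still be found. And the model, offset and censoring rule are ordinarily left to the statistical analysis plan, which is not shown.

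What remains is narrower. The harms section is not silent: it names the two quantities to be compared, and an analysis plan that followed it literally would run them without time observed. Proportions and counts are accepted harms summaries, but they are not the rates that the lead-in announces.

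**Conclusion.** The point holds as a modest improvement to the stated analysis, not as a demonstrated bias. The section promises rates and specifies two crude measures, in a trial that plans for 35% loss and permits AE-based withdrawal.

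On the document's own terms, with one loss allowance for both arms and one withdrawal rule, the consequence runs from none to some attenuation of the count ratio (1.5 to 1.43 or 1.35). Apparent safety arises only if follow-up differs by arm: a count ratio of about 0.93 at 40%/30% and 0.87 at 45%/25% when AE rates are equal. These figures rest on assumed AE rates, withdrawal probabilities, loss splits and constant hazards. They show sensitivity and are not a forecast. The case for acting is that the change is cheap and protects the safety conclusion if loss proves unequal.

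**What to change.** In Adverse event reporting and harms {22}:

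- Compare occurrences as rates per child-month under observation, using a count model with log follow-up time as offset and a cluster random effect. Count only events dated within the period that forms the denominator, so that reports from volunteers and registers after exit do not enter the numerator alone.
- Keep the proportion with at least one event as a descriptive summary, and add time to first event censored at exit beside it.
- Report follow-up time and AE-related withdrawals by arm.

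The cost is a change of wording and slightly more analysis. Visits are scheduled and dated already, so no new data collection is needed. There are two limits. The rate ratio assumes a constant AE rate, so irritation concentrated early in exposure could overstate harm in the arm with shorter follow-up; the time-to-first-event display helps to show this. And no exposure adjustment cures dropout related to AE risk that was never observed, which is why withdrawals should be shown by arm.
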